**0. SYNOPSIS**

| Study Title | Anlotinib plus Sintilimab as first-line treatment for patients with advanced colorectal cancer (APICAL-CRC): a single center, open-label, single arm, phase II study |
| --- | --- |
| Phase | Phase II |
| Objectives | To assess the safety and efficacy of a new regimen using Anlotinib plus Sintilimab as first-line treatment for patients with advanced colorectal cancer |
| Study Endpoint | Primary endpoint：  Objective response rate (ORR) by Response Evaluation Criteria in Solid Tumors (RECIST) ver1.1  Secondary endpoints:  ・Efficacy  - Disease control rate (DCR)  - Progression-free survival (PFS)  - Overall survival (OS)  ・Safety  - The incidences and types of adverse events that occur during treatment will be evaluated according to the National Cancer Institute (NCI) Common Terminology Criteria for Adverse Events (CTCAE) version 5.0.  Exploration biomarker analysis:  PD-L1 expression, TMB, molecular alteration profile, tumor immune-microenvironment, plasma exosome miRNA. |
| Study Population | According to the inclusion criteria, all mCRC patients required to be treatment-naïve, unresectable and metastatic CRCs.  **Inclusion criteria**   - Patients have histologically or cytologically confirmed advanced or recurrent CRC; - No prior systematic anti-cancer treatment and relapse or metastases was occurred more than 12 months after adjuvant chemotherapy; - Patients have measurable disease as defined by RECIST 1.1 as determined by investigator; - Patient with a history of radiotherapy at least 3 months before on the day of providing consent, but the measurable lesion should not be within the scope of radiotherapy; - Patients with age of 18-75yr; - Patients with a performance status of 0,1or 2 on the Eastern Cooperative Oncology Group.； - Patients with Life expectancy of more than 12 weeks; - Patients must have the ability to understand and sign the written informed consent voluntarily; - Female of childbearing potential who are negative in a pregnancy test within 7 days before enrollment. Both male and female patients should agree to use an adequate method of contraception (total abstinence, an intrauterine device or hormone releasing system, a contraceptive implant and an oral contraceptive) starting with the first dose of study therapy through 120 days after the last dose of study therapy. Duration will be determined when the subject is assigned to treatment.   **Exclusion criteria**   - Patients with dMMR/MSI-H; - Patients with major surgery or severe trauma within 4 weeks before the first medication; - Patients with hypersensitivity to the components in the study protocol;； - Patients who are ready to give birth or are pregnant; - Patients with brain metastases who are unable to accurately describe the condition; - Patients received immune-suppressive drugs 2 weeks before initial treatment (inhaled cortisol or other steroid hormones≤10 mg/day prednisone or equivalent pharmacophysiologic doses were excluded); - Planned live attenuated vaccine within 4 weeks prior to or during study treatment; - Patients have received anlotinib or anti-PD-1 monoclonal antibody therapy or other therapies that act on T-cell co-stimulation targets or checkpoints; - Within 6 months prior to the start of study treatment, the following diseases appeared: myocardial infarction, severe/unstable angina, NYHA grade 2 or above congestive heart failure, poorly controlled arrhythmias, etc; - Active hepatitis; - Bone marrow, liver and kidney function did not meet the requirements of chemotherapy as follows:   - Neutrophil count<1,500/mm3;  - Platelet count <80,000/mm3;  - Total bilirubin >1.5-times the upper limit of normal;  -ALT/AST>2.5-times the upper limit of normal for patients without liver  metastases; (5.0-times the upper limit of normal for patients with  liver metastases)  - Creatinine >1.5-times the upper limit of normal;   - Patients with cancers other than advanced colorectal cancer within five years prior to the start of treatment in this study. Cervical carcinoma in situ, cured basal cell carcinoma and bladder epithelial tumor were excluded; - History of substance abuse, drug use, alcohol dependence; - Patients without legal capacity or limited civil capacity; - Patients with autoimmune diseases or organ transplantation; - Other situations that the investigator deemed inappropriate for enrollment; |
| Duration of study participation | The investigational drug will be repeatedly administered until the criteria for discontinuation are met. In the event that the treatment is discontinued for reasons other than an exacerbation of the underlying disease via imaging (e.g., unacceptable side effects), tumor evaluation follow-up will continue until either an exacerbation of the underlying disease is observed via imaging or a new anticancer treatment is initiated, whichever happens first. |
| Administration method | Eligible patients were given sintilimab intravenously at a dose of 200mg on day 1, and anlotinib orally at a dosage of 12mg daily from days 1-14 every 3 weeks. Treatment was maintained until progressive disease (PD), treatment intolerance, death, or withdrawal of consent, with one cycle as 3 weeks. |
| Safety evaluation | Evaluations will be performed using CTCAE version 5.0. |
| Efficacy evaluation | The efficacy will be evaluated in accordance with RECIST version 1.1 every 6 weeks.  ・Image evaluation: computed tomography (CT) or magnetic resonance imaging (MRI) |
| Observations and tests | Physical examination, vital signs, PS, laboratory tests (hematology and biochemistry), urinalysis, tumor markers, ECG, CT of chest, abdomen, and pelvis, etc. |
| Trial Design | APICAL-CRC trial was an investigator-initiated, open-label, non-randomized, single-arm, phase II clinical trial using Simon’s minimax two-stage design. The combination of anlotinib plus sintilimab is expected to result in an improved ORR of 35%. The null hypothesis, which stated that the true ORR was 15%, would be tested against a one-sided alternative of 35%, with 80% power and a type I error rate of 5%. In the first stage, the study accrued 15 patients. If less than two response or no response was observed, the study was terminated and deemed negative. Otherwise, an additional 13 patients would be accrued for the second stage. The study was considered positive if there were more than 9 responders among the 28 patients. |
| Statistical matters | Primary endpoint (In the intention-to-treat population and in the efficacy-evaluable):  The statistical criteria for main analysis will be based on the number of patients with the best overall response of Complete Response (CR) or Partial Response (PR) according to RECIST guideline version 1.1. An accurate confidence interval based on a binomial distribution is used for calculating the proportion of confidence intervals. ORR by RECIST 1.1  Secondary endpoint  The following analyses will be performed for ITT (Intention to Treat: ITT) and efficacy-evaluable population, SP (Safety Population).   1. DCR by RECIST 1.1(In the intention-to-treat population and in the efficacy-evaluable population): Confidence intervals for DCR will be created using the exact test according to a binomial distribution. 2. PFS, OS: A survival function will be estimated using the Kaplan-Meier method. The median with the 95% CI will be estimated. 3. Incidence of adverse events: As incidence of adverse events, in addition to tabulation of the frequency of adverse events, the incidence of Grade 3 or higher adverse events will be calculated. |
| Primary investigator | [name] |
| Planned study sites | Shanghai Changzheng Hospital |

Contents

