**3.7.4.2 Imaging Evaluation**

- Screening Phase: CT or MRI scans of the chest and abdomen must be performed within 28 days before enrollment, and the measurement of the tumor should be recorded in CRF according to RECIST 1.1
- Treatment Phase：CT or MRI scan should be performed at least every 6 weeks + / - 5 days to evaluate the lesions, and the measurement of tumor should be recorded in CRF according to RECIST 1.1. Other examinations were performed according to the symptoms.
- At the end of the study：CT or MRI scan was used to evaluate the lesion, and the measurement of tumor was recorded in CRF according to RECIST 1.1. Other examinations were performed according to the symptoms。

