**5.1 Statistics analysis plan**

**5.1.1 The population for analysis**

Efficacy analysis will be conducted in the intention to treat population (ITT) and efficacy-evaluable population. The patients who did not have at least one post-baseline efficacy assessment were defined as not assessable for efficacy and were ruled out from the efficacy-evaluable population. The safety analysis included all patients in ITT population who had received at least one study medication. The analysis population of ORR refers to all patients with partial remission or complete remission determined by RECIST 1.1 in ITT population and efficacy-evaluable population.

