**5.1.3 Efficacy analysis**

Efficacy analysis will be conducted in the intention to treat population (ITT) and efficacy-evaluable population.

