**5.1.3.2** **Secondary study endpoints**

Secondary study endpoints included disease control rate (DCR, the proportion of patients who achieved a complete response, a partial response, or stable disease), progression-free survival (PFS), overall survival (OS) as well as safety.

PFS was defined as the time from therapy initiation to progression according to RECIST.

OS is defined as the time from therapy initiation to death from any cause.

Depth of response (DPR) was defined the percentage of maximum tumor reduction achieved in treatment compared with baseline. In case of CR, DPR is 100%.

Remission maintenance time was calculated in all PR or CR patients who were confirmed to meet RECIST 1.1 criteria. The duration of remission is the time from the first record to PR or Cr until death or disease progression (based on the first occurrence). As of the date of analysis, the deadline was the date of their last imaging evaluation.。

Kaplan Meier method was used to get the expected survival curve of the patients including PFS and OS.

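### OS is also to be estimated, from first dose, in an efficacy-evaluable set that drops patients who die before any post-baseline assessment, so that set's OS median is biased upward

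*Protocol*

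**What the plan says.** Under Statistical matters, the Protocol synopsis opens the secondary analyses with: "The following analyses will be performed for ITT (Intention to Treat: ITT) and efficacy-evaluable population, SP (Safety Population". The second item on that list is: "PFS, OS: A survival function will be estimated using the Kaplan-Meier method. The median with the 95% CI will be estimated". Section 5.1.3, which heads the subsections on ORR, DCR, PFS and OS, makes no exception for the time-to-event endpoints: "Efficacy analysis will be conducted in the intention to treat population (ITT) and efficacy-evaluable population".

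Section 5.1.1 defines who leaves the evaluable set: "The patients who did not have at least one post-baseline efficacy assessment were defined as not assessable for efficacy and were ruled out". No exception is made for death before the assessment.

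Section 5.1.3.2 sets the clocks. For OS: "OS is defined as the time from therapy initiation to death from any cause". For PFS: "PFS was defined as the time from therapy initiation to progression according to RECIST". Death is not named as a PFS event here, in section 2 or in section 3.7.1.

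Section 3.7.4.2 gives the timing of the assessment: "CT or MRI scan should be performed at least every 6 weeks + / - 5 days to evaluate the lesions". Footnote 4 of the flow chart gives an 8-week interval instead.

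**The concern.** Membership of the evaluable set is decided by something that happens after time zero, while survival time is counted from time zero. Anyone in the set has, by definition, lived to the first assessment. Those early weeks are guaranteed survival time, and the deaths that fall in them are removed from the curve.

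OS does not need a scan. Every treated patient contributes either a death or a censoring time, so a post-baseline assessment requirement has no purpose for this endpoint. It makes more sense for response, where an unscanned patient cannot be classified.

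What is at stake is the reported OS median. The trial has one arm, so there is no internal comparator in which the same selection would operate. The synopsis and sections 5.1.1 and 5.1.3 give the two sets equal standing, so the more favourable median could be reported as a main result without departing from the text.

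**Working it through.** **Inputs from the Protocol.** Total sample size 28 (15 + 13, section 3.1). First scheduled scan at 6 weeks with a 5-day window, taken as day 42, with day 47 as the upper end (section 3.7.4.2). OS from therapy initiation (section 5.1.3.2). Evaluable only with a post-baseline assessment (section 5.1.1).

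**Plan's own figure.** The Protocol states no median, event count or sample size for OS or PFS, so there is nothing to reproduce for these endpoints. The only design number used below is 28. An exact search for Simon's minimax design (15% against 35%, one-sided 5%, power 80%) returns 15 + 13 = 28, with type I error 0.046 and power 0.803, so 28 reproduces. That design stops at 2 or fewer responses in stage 1 and needs more than 7 of 28; the printed cut-offs differ, which is a separate matter.

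**Assumptions.** The OS median and the number of early deaths are mine and are varied below.

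**Step 1: guaranteed time.** 42 / 30.44 = 1.38 months; 47 / 30.44 = 1.54 months. If the 8-week interval in the flow-chart footnote applied, 56 / 30.44 = 1.84 months.

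**Step 2: expected shift under a plain exponential.** For patients who survive to t0, the median solves S(t) / S(t0) = 0.5, which gives t = m + t0. With m = 20 months and t0 = 1.38, the evaluable-set median is about 21.4 months, a shift of about 1.4. The expected number of deaths by day 42 is 28 × (1 − 2^(−1.38/20)) = 1.3. For medians of 6, 12, 18 and 24 months, the same formula gives 4.1, 2.2, 1.5 and 1.1 early deaths.

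**Step 3: shift for a given number k of early deaths.** Suppose k of 28 patients die before day 42 and the rest follow an exponential from day 42, scaled so that the ITT median is m. With f = k/28, the hazard is h = ln(2(1 − f)) / (m − 1.38), and the evaluable-set median is 1.38 + ln 2 / h.

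| k of 28 | ITT survival at 6 weeks | ITT median 6 | ITT median 12 | ITT median 24 |
| --- | --- | --- | --- | --- |
| 0 | 100% | 6 | 12 | 24 |
| 1 | 96% | 6.3 (+4%) | 12.6 (+5%) | 25.3 (+5%) |
| 2 | 93% | 6.6 (+9%) | 13.3 (+11%) | 26.7 (+11%) |
| 3 | 89% | 6.9 (+15%) | 14.1 (+17%) | 28.4 (+18%) |

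The cells give the evaluable-set median in months. If every evaluable patient is first assessed on day 42, evaluable-set survival at 6 weeks is 100% by construction in every row.

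**Step 4: cross-check.** The simpler formula m × ln(0.5 × (1 − k/28)) / ln 0.5, with m = 20, gives 21.1, 22.1 and 23.3 months for k = 1, 2 and 3 (+5%, +11%, +16%). Both constructions agree closely.

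**Step 5: PFS as written.** The event is RECIST progression only. A patient who dies with no post-baseline assessment has no event. If that patient is censored before the first recorded progression, the patient is in no risk set at which the curve drops, and deletion leaves the Kaplan-Meier estimate unchanged. The PFS shift is then zero. It becomes upward only if death is counted as an event.

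**The case against.** The strongest reply is that ITT curves are already planned and named first, that section 5.1.1 states the exclusion openly, that the trial decision rests on ORR alone, and that which set leads is often settled in a SAP. It can be added that, within the synopsis list, only DCR carries its own evaluable-set label. Much of this stands: it limits the consequence to a parallel estimate of a secondary endpoint. It does not remove the point. Section 5.1.3 applies both sets to all efficacy analysis, and the difficulty lies in what the Protocol prescribes, not in something left unsaid.

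Early deaths may also be few. Entry requires a life expectancy of more than 12 weeks, although ECOG 2 is allowed. With a 20-month exponential median, 1.3 early deaths are expected, so 2 or 3 would be above expectation. An unscheduled earlier scan also makes a patient evaluable, so 6 weeks is not a fixed guaranteed period.

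A reader might infer more than the text supports:
- **That all survival medians are biased.** Only the evaluable-set estimates are; ITT keeps the early deaths.
- **That PFS is biased in the same way.** The written definition omits death, so it is not.
- **That everyone who deteriorates or stops early is removed.** The synopsis continues tumour evaluation after stopping for reasons other than imaging progression, and section 3.7.4.2 asks for a scan at the end of study, so many such patients would stay evaluable.
- **That early losses add to the shift.** They are censored early, and removing them does not move the median.
- **That the evaluable-set median is always the more favourable.** An unassessed patient still followed for survival (sections 3.7.4.1 and 3.8.5) may die late, and deleting that patient could lower the median.

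**Conclusion.** The point holds for OS in the efficacy-evaluable set. As written, the Protocol deletes patients who die before their first post-baseline assessment while counting time from first dose, and it gives the result the same standing as ITT. The direction is upward whenever such deaths occur. The size cannot be taken from the document: it is about 1.4 months in expectation under an assumed 20-month exponential median, about 5% to 17% if 1 to 3 of 28 patients die early, and zero if none do. Reading the efficacy assessment as the scan at about 6 weeks is an inference from the RECIST imaging schedule.

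The ITT medians and the ORR decision are unaffected. PFS is affected only if death is treated as an event, which the current definition does not say. This should be corrected because the cure is simple, but it concerns a supportive estimate of a secondary endpoint.

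**What to change.** In the synopsis (Statistical matters) and in sections 5.1.1 and 5.1.3, limit the efficacy-evaluable set to ORR and DCR. State that OS and PFS are estimated in all ITT patients who received at least one dose, from first dose, with no requirement for a post-baseline assessment. This wording serves PFS whether or not death is counted as an event.

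If an evaluable-set curve is still wanted, use a landmark: start the clock at the first scheduled assessment, include only patients still at risk then, and label the curve descriptive. The 6-week and 8-week intervals must be reconciled before the landmark can be fixed.

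The cost is a few sentences of wording and one supportive analysis dropped or relabelled. No extra patients or data are needed. The reported OS median may be slightly less favourable.

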**1.1 Advanced Colorectal Cancer**

Colorectal cancer (CRC) ranks the third in terms of cancer incidence and is also the most common malignant tumors in the digestive system, which is a serious threat to human health[1]。In China, approximately 380,000 colorectal cancer cases were newly diagnosed and 200,000 cases dead annually. The incidence and mortality of colorectal cancer patients in city area are higher than that of rural area. For example, colorectal cancer ranks the second in terms of cancer incidence in Shanghai. Almost 1/4 patients were developed advanced stage at the time of diagnosed, half of CRC patients could develop recurrence and distant metastasis, resulting in poor prognoses and short survival[2-3]。

**1.2 Treatment Strategy for advanced CRC**

For advanced or metastatic CRC, chemotherapy is one of the main treatment methods, which plays an important role in controlling the disease, prolonging the survival period and improving the quality of life. There are three commonly used chemotherapy drugs: fluorouracil, oxaliplatin and irinotecan. The researches have not made breakthrough progress on other chemotherapy drugs. In addition, targeted therapy also plays an important role in the treatment of advanced CRC. At present, the combination of chemotherapy and targeted therapy is the standard-of-care recommended by NCCN guidelines [3-5]. Recently, the rise of immune checkpoint blockade inhibitor provides a new field and direction for immunotherapy among advanced CRC patients.

**1.3 Immune checkpoint inhibitor and CRC**

Immune checkpoint inhibitor is currently a hot spot in the treatment of malignant tumors, and has achieved remarkable curative effects in lung cancer, liver cancer, urinary tract malignant tumors, malignant melanoma and hematologic malignant tumors. Immunotherapy has greatly improved the prognosis of cancer patients. Besides, immune checkpoint therapy is the first treatment regimen for pan-tumor approved by the FDA based on molecular characteristics (dMMR/MSI-H).

Based on KEYNOTE016 and CHECKMATE142 studies, pembrolizumab and nivolumab-based immunotherapy regimens have been recommended for the treatment of advanced colorectal cancer with dMMR/MSI-H, especially in patients resistant to chemotherapy plus anti-EGFR/VEGF targeted therapy, with higher recommended level [6]. Currently, the main dominant population of immune checkpoint therapy was advanced CRC patients with dMMR/MSI-H. However, dMMR/MSI-H colorectal cancer only accounts for 3~5% of all advanced CRC patients, and the vast majority of pMMR/MSS patients cannot obtain clinical benefit from immunotherapy alone. In order to change this treatment dilemma, many clinical attempts have been made. For example, the combinations of immunotherapy with other therapeutic means (such as small molecule TKI, chemotherapy, radiotherapy, etc.) were explored to promote the sensitivity to immunotherapy among this “Cold tumor”. Unfortunately, most above trials have failed. The Phase-II trial showed that 8% of advanced CRC patients could achieved PR after received Atezolizumab combined with cobimetinib, with a DCR of 31%. The results make researchers expect the efficacy of subsequent phase III study (IMblaze-370). However, IMblaze-370 did not reach primary endpoints, showing whether Atezolizumab alone or Atezolizumab combined with cobimetinib could not bring significantly more clinical benefit than regorafenib, with the mOS of 7.1m, 8.9m, and 8.5m, respectively [7]. Another phase II study enrolling 30 treatment-naïve advanced CRC patients who received Pembrolizumab combined with mFOLFOX6 observed 1 patient with CR, 15 patients with PR. The efficacy of this combination regimen seems comparable, but not superior to conventional chemotherapy plus targeted therapy. More importantly, 2 out of 6 patients develop G3 granulomyle deficiency fever and 1 G4 neutropenia in safety dose exploratory analysis. MODUL study explored whether the addition of Atezolizumab to conventional fluorouracil plus bevacizumab as a maintenance regimen could bring more clinical benefit. After 18.7 months of follow-up, there was no significant difference between the two groups in either PFS or OS, and the addition of Atezolizumab to standard FP/bevacizumab first-line maintenance regimen did not improve PFS and OS in advanced mCRC patients.

All in all, immunotherapy has limited benefit among patients with advanced colorectal cancer, particularly in the pMMR/MSS cohort. In order to mutate this shackle, researchers have carried out unremitting exploration. A study published in by 2019 ASCO-GI seems to give us a glimmer of light, in which the use of durvalumab (PD-L1 antibody) plus tremelimumab (CTLA-4 antagonist) versus best supportive care (BSC) could prolong OS in patients with advanced colorectal cancer who did not respond to existing treatments. This is the first study in which immunotherapy could significantly more benefit for colorectal cancer patients who have not undergone MMR screening. However, even using dual immunotherapy, mOS duration was only 6.6 months, which was only 2.5 months longer than that of the BSC alone, which is of little significance for clinical practice.

At the ASCO meeting in June 2019, the REGONIVO study rekindled hope for immune checkpoint treatment for advanced colorectal cancer with pMMR/MSS. The REGONIVO study was initially conducted in multiple advanced gastrointestinal tumors, including colorectal cancer, gastric cancer, and liver cancer, with regorafenib dose-ramped in the 2 drugs used and nivolumab using a fixed 3 mg/kg q2w. Efficacy data on the colorectal cancer and gastric cancer showed an overall ORR of 40% in patients who underwent multiple lines of therapy, and an ORR of 36%, 44% for colorectal cancer, and gastric cancer, respectively. More importantly, 33% of pMMR/MSS CRC patients achieved CR or PR. This efficacy seems to be limited, but the significance of the REGONIVO study is significant compared to regorafenib monotherapy in the CORRECT and CONCUR trials with ORRs of 1%, 4% in CORRECT and CONCUR trials, respectively [8, 9]. The ORR of REGONIVO study also was better that of nivolumab in CHECKMATE142 trial, which also had only 10 % ORR in MSS. The PFS of REGONIVO study was 6.3 months in colorectal cancer, which was also a considerable advantage when compared with 1.9 months, 3.2 months in the CORRECT and CONCUR trials. In REGONIVO trial, almost all CRCs patients had received antiangiogenic therapy, and the patients could achieve objective remission regardless of RAS wild type, RAS mutant type, PD-L1 positive or negative expression, indicating that the promising prospect of REGONIVO regimen.

In the preclinical experiment of REGONIVO trial [10], the researchers found that regorafenib could inhibit colony-stimulating factor receptor (CSF-1R) and reduce F4/80+ immune cells in CT26CRC tumors of immunocompromised nude mice growing, suggesting immunomodulatory effects related to antitumor activity. Moreover, regorafenib combined with anti-PD-1 showed a more significant synergistic anti-tumor effect in in vitro experiments. These preliminary studies provide a theoretical basis and support for clinical translational research, suggesting that it is possible that regorafenib increased tumor sensitivity to immune checkpoint therapy. Other small molecule multi-target TKI inhibitors also have similar effects and have been validated in other tumors. A clinical trial using anlotinib combined with sintilimab (anti-PD-1 monoclonal antibody) in the first-line treatment of advanced non-small cell lung cancer, provided an objective response rate of 72.2% and a disease control rate of 100%. This study also enhances us that the immunotherapy-based regimen moves to the front-line could bring more efficacy, because the efficacy of immunotherapy is closely related to the integrity of immune function. Although REGONIVO trial has achieved great success in the treatment of advanced colorectal cancer, only 1/3 patients have achieved objective response, which may be related to late-line use. The first-line treatment effect of advanced colorectal cancer is significantly higher than that of late-line, so we consider that the appropriate regimen in advanced first-line patients may achieve better clinical efficacy and avoid the adverse effects of chemotherapy. We design this trial to explore the efficacy of small molecule multi-target TKI inhibitors (Anlotinib) combined with anti-PD-1 antibodies (Sintilimab) as the first-line regimen for advanced colorectal cancer.

1. **Objective**

To assess the safety and activity of Anlotinib in combination with Sintilimab among treatment-naïve advanced CRC patients.

Primary endpoint：Objective Response Rate (ORR, complete or partial response according to RECIST version 1.1).

Secondary study endpoints: Disease Control Rate (DCR, the proportion of patients who achieved a complete response, a partial response, or stable disease), Progression-Free survival (PFS), overall survival (OS) as well as safety. PFS was defined as the time from therapy initiation to progression according to RECIST. OS is defined as the time from therapy initiation to death from any cause.

Exploration study endpoints: biomarker analysis including PD-L1 expression, TMB, molecular alteration profile, tumor immune-microenvironment, plasma exosome miRNA.

1. **Method**
   1. **Study design**

APICAL-CRC trial was an investigator-initiated, open-label, non-randomized, single-arm, phase II clinical trial using Simon’s minimax two-stage design. The combination of anlotinib plus sintilimab is expected to result in an improved ORR of 35%. The null hypothesis, which stated that the true ORR was 15%, would be tested against a one-sided alternative of 35%, with 80% power and a type I error rate of 5%. In the first stage, the study accrued 15 patients. If less than two response or no response was observed, the study was terminated and deemed negative. Otherwise, an additional 13 patients would be accrued for the second stage. The study was considered positive if there were more than 9 responders among the 28 patients.

- 1. **Single-arm**

This trial design is a single-arm study without control group.

- 1. **Participants**

According to the inclusion criteria, all patients required to be treatment-naïve advanced CRCs

